# Reducing readmission rates for individuals discharged from acute psychiatric care in Alberta using peer and text message support: Protocol for an innovative supportive program

**DOI:** 10.1186/s12913-022-07510-8

**Published:** 2022-03-12

**Keywords:** Mental health, Hospital readmission, Text4Support, Peer support

## Abstract

**Background:**

Individuals discharged from inpatient psychiatry units have the highest readmission rates of all hospitalized patients. These readmissions are often due to unmet need for mental health care compounded by limited human resources. Reducing the need for hospital admissions by providing alternative effective care will mitigate the strain on the healthcare system and for people with mental illnesses and their relatives. We propose implementation and evaluation of an innovative program which augments Mental Health Peer Support with an evidence-based supportive text messaging program developed using the principles of cognitive behavioral therapy.

**Methods:**

A pragmatic stepped-wedge cluster-randomized trial, where daily supportive text messages (Text4Support) and mental health peer support are the interventions, will be employed. We anticipate recruiting 10,000 participants at the point of their discharge from 9 acute care psychiatry sites and day hospitals across four cities in Alberta. The primary outcome measure will be the number of psychiatric readmissions within 30 days of discharge. We will also evaluate implementation outcomes such as reach, acceptability, fidelity, and sustainability. Our study will be guided by the Consolidated Framework for Implementation Research, and the Reach-Effectiveness-Adoption-Implementation-Maintenance framework. Data will be extracted from administrative data, surveys, and qualitative methods. Quantitative data will be analysed using machine learning. Qualitative interviews will be transcribed and analyzed thematically using both inductive and deductive approaches.

**Conclusions:**

To our knowledge, this will be the first large-scale clinical trial to assess the impact of a daily supportive text message program with and without mental health peer support for individuals discharged from acute psychiatric care. We anticipate that the interventions will generate significant cost-savings by reducing readmissions, while improving access to quality community mental healthcare and reducing demand for acute care. It is envisaged that the results will shed light on the effectiveness, as well as contextual barriers and facilitators to implementation of automated supportive text message and mental health peer support interventions to reduce the psychological treatment and support gap for patients who have been discharged from acute psychiatric care.

**Trial registration:**

clinicaltrials.gov, NCT05133726. Registered 24 November 2021

**Supplementary Information:**

The online version contains supplementary material available at 10.1186/s12913-022-07510-8.

## Background

Avoidable hospital readmission is a growing concern in health systems across the world. Readmissions often lead to significant physical, psychological, and financial impact on patients and their families. The health system is also affected as there are limited infrastructural, human, and financial resources [1, 2]. This is true in the era of the COVID-19 pandemic, which has seen many hospitals overwhelmed by rising emergency department (ED) presentations [3–5]. Consequently, there is a renewed interest to seek out solutions to mitigate avoidable readmissions, particularly in acute care.

People with psychiatric disorders have the highest early readmission rates among all hospitalized patients [6–8]. Early readmission is defined as readmission within 30 days of previous discharge [6]. Whereas deinstitutionalization of care and transition to community-based mental health care has been an approach of focus for decades [9–11], early hospital readmission rates remain high. Unmet need for psychological treatment and the limited human resources to address this gap is a major cause of high 30-day readmissions rates in acute psychiatry units [6].

In Alberta, Canada, about 8.4–11.9% of residents have a mental illness, but less than 25% of these individuals report that their mental health care needs were fully met [12]. This is despite the statistic that almost 70% of people with mental illnesses had accessed and utilized a provincial mental health service the year before, according to a 2014 mental health gap assessment report [12]. The greatest unmet need cited is the lack of sufficient, accessible, and affordable counselling. Their next greatest concern was an unmet need for tailored information on their own mental health challenges. This is despite several interventions provided by the provincial health authority, Alberta Health Services (AHS), to address addiction and mental health challenges through their community health clinics, and free-standing addiction and mental health (AMH) facilities, among others. Interestingly, 86% of AHS direct providers believe that they provide sufficient information to clients [12]. This discrepancy between service recipients and community providers’ perspectives reinforces concerns that services may not be well tailored to the diverse perceived needs of various groups. A consequence of this gap is the high demand for more specialist services and high readmissions after discharge from a recent hospital stay, leading to higher cost of health services [12, 13]. One study reports 90-day readmission rates of up to 14.0%, with the median time to readmission being 24 days [14]. More findings from the 2014 mental health gap assessment revealed that current management strategies are reactive, with system resources heavily invested in inpatient, residential and crisis services. Technology was noted to be under-utilized in the province. Reducing the felt need for hospital visits by providing alternative effective care will mitigate the existing strain on healthcare, human and financial resources due to mental illness [12, 13]. To address this, we propose an innovative program which augments mental health peer support, which is provided by individuals with lived experience of mental illness, with an evidence-based supportive text messaging program developed using the principles of cognitive behavioral therapy (CBT) [13].

### Components of the innovation

Peer support is valued in recovery-oriented models [15] of mental illness and increasingly implemented [16]. Evidence indicates positive effects, including lower inpatient service use, better relationships with providers and increased engagement. Peer Support Workers (PSWs) who are in recovery and have lived experience with mental illness will play central roles in this study, including delivering some of the interventions proposed. PSW activities will include supportive face-to-face visits, interactive phone calls/texts/zoom meetings with patients, advocacy, connecting patients with community resources, and experiential sharing. PSWs will be actively engaged through all provincial practice councils and are already embedded within many Alberta AMH programs. Evidence also shows that providing peer support to others may also benefit the PSWs by enhancing their own feelings of competence and personal value [17–22].Text4Support will be provided through ResilienceNHope, which is an online application site (https://application.resiliencenhope.com/). It is a low-cost, evidence-based, supportive text messaging program which will be coupled with or without mental health peer support services to reduce the psychological treatment and support gap for study participants who have been discharged from acute psychiatry care into community. Starting a day after enrolment, intervention-group participants will receive daily unidirectional (no-reply) supportive text messages. The text messages will be written by cognitive behavior therapists in partnership with individuals with lived experience of mental illness. The Text4Support program was developed based on knowledge from randomized controlled trials conducted in Ireland [23, 24] and Alberta [13, 25]. The program is also based on knowledge gained from the highly successful award winning Text4Mood program in Alberta’s North Zone which improved the psychological treatment gap and was effective [26] and scalable (i.e., > 10,000 recipients within 6 months). The Text4Hope program was launched in Alberta during the COVID-19 pandemic which was also effective and scalable (> 48,000 subscribers within 3 months) [27–37]. Text4Support provides CBT-based and diagnosis-specific daily supportive text messages for 6 months. Some examples of the text messages are:What lies behind you and what lies before you are tiny matters compared to what lies within you. Have faith in yourself, and success can be yours.There are 2 days in the week we should not worry about, yesterday and tomorrow. That leaves today. Live for today.Stumbling blocks can become steppingstones to a better life. You can turn adversities into opportunities. Don’t be discouraged by today’s problems.Letting go of resentment is a gift you give yourself. It will ease your journey immeasurably. Make peace with everyone, and happiness will be yours.

Determination of diagnosis-specific approach was based on an analysis of Alberta service data, which suggested that diagnostic clusters for individuals discharged from acute psychiatry units into community for follow-up fell into six major categories: mood disorders, anxiety disorders, schizophrenia and other psychotic disorders, substance use disorders, adjustment disorders and personality disorders. Thus, text message content will focus on two dimensions. First, general content that is indicated regardless of symptomatology will be presented, including messages of self-care, social support, hope, affirmation, and recovery. Second, specific content will be provided that focuses on management of symptoms related to the specific conditions described above (e.g., activity scheduling in depression). As a component of scalability and inclusiveness, text message content can also be customized based on end-user characteristics. Specifically, we will explore content that is sensitive to needs based on age group, cultural identity, gender identity, and non-English language communication. This serves to enhance access for diverse groups, many of whom may be marginalized or underserved. In addition, individuals identified to be most at-risk of readmission to hospital will be offered mental health peer support. Matching an individual to a PSW will also consider the individual’s choice, demographic characteristics and factors, such as cultural and gender identity. These will be explored as the project is scaled up and the pool of PSWs increases.

### Study aim

This study is designed to address gaps in care/support available at the community level for individuals discharged from inpatient psychiatry units and referred to community mental health services for follow-up. We aim to reduce the psychological treatment and support gap for those who have been discharged from acute care and are scheduled to receive mental health and psychiatric treatment from AMH services after a long wait. Unpublished preliminary data from these pilot interventions provide evidence that psychiatric readmissions and emergency department visits are reduced by 10-25%. Given these results, if implemented at scale in Alberta could result in cost-savings for individuals and the province.

## Methods and analysis

This study will both evaluate the effectiveness of this intervention as well as implementation context and outcomes. Implementation context is “the set of circumstances or unique factors that surround a particular implementation effort” [38], while implementation outcomes are “effects of deliberate and purposive actions to implement new treatments, practices, and services” [39]. Implementation outcomes are indicators of implementation efforts, and are distinct from service or clinical outcomes [39].

The Consolidated Framework for Implementation Research (CFIR) will provide an overarching guidance to design, implementation, and evaluation by examining outer/inner contexts, intervention characteristics, and stakeholders involved as well as the process of implementation [40].

Further, using the Reach-Effectiveness-Adoption-Implementation- Maintenance (RE-AIM) framework [41], we will: (1) examine the reach of the interventions, i.e., text and peer support; (2) evaluate their effectiveness; (3) gauge support for their adoption; (4) evaluate fidelity in implementation; and (5) document the maintenance (sustainability) of implementation post-trail.

### Study design

A pragmatic stepped-wedge cluster-randomized approach will be applied, providing Text4Support and Peer Support Service (PSS) to 10,000 participants recruited across 9 acute care sites and day hospitals across Alberta as the clustered unit of randomization (Fig. 1). The design reconciles constraints under which policy makers and service managers operate with the need for rigorous scientific evaluations. In a stepped-wedge study, the design is extended so every cluster provides pre-post observations, and switches from control to intervention exposure but not at the same time-point [42].

**Fig. 1 Fig1:**
[figure not shown]
Number of new and total recruits expected in each cluster and period

The design is a preferable study design when:Evidence supports the intervention (e.g., known to be effective at individual level but uncertain about policy level), or there is resistance to parallel designs in which only half of the clusters receive the intervention.The intervention is a service delivery or policy change that can be implemented with the primary outcome, or at least some important outcomes available from routinely collected data (e.g., reduced readmission rates, acute care cost and no- show rates, routinely collected by AHS and primary study outcomes).The intra-cluster correlation is anticipated as high or cluster sizes large, so a cross-sectional stepped-wedge design is likely more efficient than a parallel cluster design.

This design has been successfully implemented with complex programs and change management involving large-scale programs in many countries [43, 44]. The study also adheres to checklists from the EQUATOR network ([45–47] (see Additional files 1 and 2).

### Participant recruitment

Individuals who have been diagnosed with a mental illness, are ready for discharge from an inpatient psychiatry unit that is part of the study, are 18 to 65 years of age, have a mobile device, can read English text messages, and can provide informed written consent will be eligible for the study. Recruitment will commence in February 2022 and will be done by the research team with physicians and other providers at the various sites. Participants should have a mobile device capable of receiving text messages. Participants will be ineligible if they know they will be based out of town during the 12-month follow-up period.

### Sample size considerations

We anticipate a reaching a target sample of 10,000. This figure is about 50% of expected psychiatric discharges, based on the 2018 administrative data (*n* = 20,747) [48]. We decided not to present detailed power analysis for sample size, which is controversial for stepped-wedge design approaches [49]. Further, our study is a pragmatic trial aiming to cause change in real-world conditions, rather than an explanatory trial which aims to study under ideal conditions. Thus, our approach is guided by the Pragmatic-Explanatory Continuum Indicator Summary 2 (PRECIS-2) toolkit with which we aim to align with the higher scores in pragmatism [50].

With our intended 5 randomized clusters and targeted overall project clinical population sample size of 10,000 (including accounting conservatively for 20% patient dropout and 10% dropout for PSWs), we are confident that our sample sizes are more than adequate as we expect at least medium-effect sizes, consistent with our prior results with supportive text messaging programs in Alberta [51].

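### The sample is called adequate on the strength of a medium effect size that cannot describe 30-day readmission, the primary outcome

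*Protocol article*

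**What the plan says.** All places are in the protocol article.

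- **Sample size considerations** sets the target as a share of throughput: "We anticipate a reaching a target sample of 10,000", and "This figure is about 50% of expected psychiatric discharges, based on the 2018 administrative data" (20,747 discharges). The authors then write: "We decided not to present detailed power analysis for sample size, which is controversial for stepped-wedge design approaches".
- The same section ends with a positive claim. It opens "With our intended 5 randomized clusters and targeted overall project clinical population sample size of 10,000", states that allowance for dropout is included, and concludes: "we are confident that our sample sizes are more than adequate as we expect at least medium-effect sizes". The medium effect is attributed to the group's earlier text-messaging results. The outcome on which those results were obtained is not named.
- **Abstract, Methods** makes the number of psychiatric readmissions within 30 days the primary outcome.
- **Study aim** gives the only effect on readmission in the document. Unpublished pilot data are said to show that "psychiatric readmissions and emergency department visits are reduced by 10-25" per cent.
- **Background** gives the only figures from which a base rate can be inferred: "One study reports 90-day readmission rates of up to 14.0%, with the median time to readmission being 24 days".
- **Study design** names 9 sites as the unit of randomization, against the 5 clusters above, and speaks of providing the interventions to 10,000 participants.

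**The concern.** Leaving out a power calculation is not the issue, since the article discloses it and a fuller plan may supply one. The issue is that the article then asserts a design property and gives a reason for it. That reason, a medium standardized effect, is hard to square with a 10-25% relative reduction in an uncommon binary event.

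If the reason does not apply to readmission, the article gives no support for adequacy on the outcome that decides the trial. A non-significant result from a trial described in these terms would be read as evidence of no benefit, even where the trial had little chance of detecting an effect of the size its own pilot reports.

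**Working it through.** **1. The stated figure.** 10,000 / 20,747 = 48.2%, which matches the article's rough half of discharges. It is a feasibility figure. No alpha, power, base rate or intracluster correlation (ICC) is given, so it cannot be reproduced as a power-based number. For a standardized mean difference of 0.5, two-sided 5% and 80% power, an individually randomized comparison needs n = 2(1.96 + 0.84)² / 0.5² ≈ 63 per arm. For a truly medium effect the sample is therefore ample.

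**2. Base rate (assumption).** If 14.0% are readmitted by 90 days and the median time is 24 days, about half of them, 7%, are readmitted by day 24. The 30-day rate is then at least about 7% and at most 14%. I use 7-14%. The source figure is an upper value, so lower rates are possible and would make the picture worse.

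**3. What 10-25% is in standardized terms.** h = 2·asin(√p₁) − 2·asin(√p₂).
- Smallest: p₁ = 0.07, p₂ = 0.063, h = 0.028.
- Largest: p₁ = 0.14, p₂ = 0.105, h = 0.107.

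In reverse, p₂ = sin²(asin√p₁ − h/2).
- h = 0.5: 7% falls to 0.03% (a 99% reduction) and 14% falls to 1.8% (87%).
- Even a small effect, h = 0.2: 7% falls to 2.8% (60%) and 14% falls to 7.8% (44%).

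The scale does not rescue the claim. A difference of 0.5 on the logit scale is an odds ratio of exp(−0.5·π/√3) = 0.40, which takes 8% to 3.4%, a 58% reduction.

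**4. Best case, no clustering, 5,000 v 5,000, two-sided 5%.** Power ≈ Φ(δ/SE − 1.96), with δ = p₁ − p₂. At base 14% and a 10% reduction, δ = 0.014 and SE = √[(0.1204 + 0.1101)/5000] = 0.0068, giving 54%. At base 7%, 8% and 10% the power is 29%, 33% and 40%. At a 25% reduction it is 95.5% or more.

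**5. Stepped wedge.** Assumptions: 5 clusters, 6 equal periods with one cluster crossing at each step (Fig. 1 is not available to me), 10,000 observations in all (333 per cluster-period), and a normal approximation. SE is the generalized least squares standard error from the Hussey-Hughes model, extended by an exchangeable cluster-period effect with cluster autocorrelation (CAC) 1.0 or 0.8. The outcome variance is p̄(1 − p̄), with p̄ the mean of the two rates. Example: base 8%, 25% reduction, ICC 0.01, CAC 1: δ = 2.0 points, SE = 0.90 points, power 61%.

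| Reduction, base rate | ICC 0 | ICC 0.001, CAC 1 | ICC 0.01, CAC 1 | ICC 0.01, CAC 0.8 | ICC 0.05, CAC 0.8 |
|---|---|---|---|---|---|
| 10%, base 8% | 20% | 15% | 14% | 10% | 6% |
| 25%, base 7% | 76% | 62% | 55% | 37% | 17% |
| 25%, base 8% | 82% | 68% | 61% | 42% | 19% |
| 25%, base 10% | 90% | 78% | 71% | 51% | 23% |
| 25%, base 14% | 97% | 91% | 86% | 67% | 31% |

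Over base rates of 7-14%, power for a 10% reduction is 6-32% in every scenario. For 17.5%, the middle of the pilot range, it is 10-47% with base 7-10% and ICC at least 0.001.

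**6. Sensitivities** (base 8%, ICC 0.01, CAC 1 unless stated).
- Small-sample reference for few clusters, 25% reduction: 61% with z, 56% with t on 19 df, 34% with t on 3 df.
- 10,000 treated plus as many control observations (20,000 in all): 23% at a 10% reduction, 58% at 17.5%, 88% at 25%. The last falls to 55% at CAC 0.8.

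**The case against.** A reader might infer that the trial is underpowered across the whole 10-25% range. The documents do not support that.

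- They fix no 30-day rate, ICC, CAC or period sizes. At a 25% reduction, power passes 80% if there is no clustering (base 8% or more), or at a 14% base with CAC 1 or ICC 0.001.
- Study design can be read as 10,000 treated participants, with control observations from administrative data added on top. Power would then be higher.

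A reader might also deduct the 20% dropout and work with 8,000. Sample size considerations says dropout is already allowed for, and the primary outcome comes from administrative data, so that deduction is not warranted.

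Two further points are fair. The 10-25% is pilot evidence and is not declared as the design effect. The medium effect is tied to earlier programs and not expressly to readmission, so reading the adequacy claim as covering the primary outcome is an inference.

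These points limit what can be said about power at the upper end. They leave the main point untouched: the claim exempts no outcome, 10-25% is the only readmission effect on offer, and the mismatch in step 3 needs no ICC, period count or cluster size. The low power at 10% also survives every assumption tried. It is at most 54% with 10,000 individually randomized, and 23% in the 20,000-observation case of step 6.

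**Conclusion.** The concern holds in this form: the reason given for adequacy does not apply to the primary outcome. On the protocol's own readmission figure the effect lies below even the conventional small size, and a medium effect would require nearly all readmissions to disappear. This rests on the assumed 7-14% base rate and on reading medium as h = 0.5. On the logit scale the gap is smaller (58% at an 8% base), but still well beyond 25%.

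On power, under the stepped-wedge assumptions listed, it is low at a 10% reduction, mostly low in the middle of the range, and undetermined at 25%. A small-sample correction for 5 clusters would lower all of these figures. The adequacy sentence should not stand as written.

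**What to change.** Rewrite the closing paragraph of Sample size considerations. Enrolment need not change.

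1. Remove the adequacy claim and the medium effect as the basis for the primary outcome. Confine the medium-effect statement to the outcomes on which it was observed.
2. State the power, or the minimum detectable reduction, for 30-day readmission over 10-25%. Use a base rate, ICC and CAC from administrative data, the actual cluster-period sizes and a small-sample correction. The figures above rest on assumptions and should not be printed as the trial's own.
3. Say whether the 10,000 includes control-period observations, and reconcile 5 clusters with 9 sites.
4. State that a non-significant result does not exclude a reduction within the part of the 10-25% range where power is low.

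The cost is one paragraph and a calculation from administrative data. The stated adequacy becomes less favourable.
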